## Abstract

**Background:**

Hospitalizations are common among individuals with substance use disorders (SUD) and represent crucial opportunities to engage patients in treatment. Quality efforts to increase SUD treatment access in hospital settings must be paired with interventions that support linkage to follow-up SUD and medical care. However, the best way to support patients with SUD during transitions of care after hospitalization is unknown.

**Methods:**

The IntACT pilot study is a single-site randomized controlled trial that aims to assess the feasibility and preliminary effectiveness of a primary care-based Interdisciplinary Addiction Care Transition (IntACT) team. IntACT deploys from a partnering primary care clinic to the hospital to meet patients with SUD while they are admitted, then follows them after discharge for four months to facilitate linkage to and retention in follow-up care. The pilot study will randomize 75 hospitalized patients with SUD to receive IntACT or Usual Care, assessing both implementation and effectiveness outcomes over a six month study period. Primary outcomes include implementation measures (e.g., reach, acceptability, feasibility, and cost) assessed using a mixed methods approach, as well as preliminary measures of effectiveness including successful linkage to follow-up medical and/or SUD care after hospitalization and retention in treatment. Secondary effectiveness measures include time to first post-discharge follow-up visit, substance use patterns, and acute care utilization (e.g., hospital readmissions). The IntACT study will also enroll 20 clinicians from hospital and outpatient settings who interact with IntACT while providing patient care to provide input on intervention feasibility, appropriateness, and acceptability. Study design and procedural elements will also be assessed for feasibility and acceptability.

**Discussion:**

Identifying promising interventions to support transitions to follow-up SUD and medical care following hospitalization is imperative to increase SUD treatment access and improve care quality. The IntACT pilot study evaluates the feasibility of a novel, potentially scalable team-based care transition intervention, gathering implementation data from both patients and clinicians who are exposed to the intervention. The results of this pilot study will inform intervention refinement for a future fully-powered clinical trial, as well as other implementation and research efforts supporting care transitions for people with SUD.

**Trial registration:**

Clinicaltrials.gov NCT07575373

## Background

Deaths attributable to the overdose public health crisis have cumulatively surpassed 700,000, with an American dying from drug overdose every 7.5 minutes in 2025 [1]. In 2022, opioid overdose was responsible for an estimated 3.1 million years of life lost in the US, [2] while alcohol directly contributes to approximately 178,000 deaths annually [3]. Despite the availability of effective pharmacotherapies, treatment for substance use disorders (SUD) is not accessed by the vast majority of individuals who could benefit [4, 5] As a result, expanding access to SUD treatment is a public health imperative for the US.

Hospitals have emerged as important venues for expanding access to SUD treatment. It is estimated that 1 in 9 hospitalized patients has a SUD, [6] and 25% of people with opioid use disorder have experienced a medical hospitalization in the past year [7]. Hospital-based SUD care models like addiction consult services and buprenorphine initiation protocols have enabled many hospitals to significantly expand access to inpatient SUD care initiation, particularly with medication treatment [8–11]. Despite the success of these models within the hospital, sustained treatment engagement after hospital-based medication initiation is modest, [8,12] and the best way to connect patients to long-term medical and SUD care after hospitalization remains unknown. Further, the period immediately following hospital discharge is associated with an acutely elevated risk of mortality for patients with OUD, [13,14] making identification of effective models to support patients through these transitions a pressing need.

While various post-hospitalization care transition models have been implemented on a small scale (i.e., within a single hospital or clinic), few have been rigorously studied [15,16]. Existing models include hospital-based addiction consult services, [8,9,17,18] discharge protocols for hospital teams, [19–22] transitional care interventions like peer navigation and care management, [23–27] and outpatient-based interventions like bridge clinics and post-discharge outreach [21,28–31]. Many of these interventions are designed to work within one part of the care transition spectrum, rather than across inpatient, transitional, and outpatient settings. For example, a hospital-based addiction consult team might initiate buprenorphine for opioid use disorder and assist with scheduling follow-up appointments, but once the patient leaves the hospital the consult team no longer provides support. Novel interventions that are designed to operate across inpatient and outpatient care settings with a single care team may improve care linkage and early retention in treatment. Whether these types of models are feasible and acceptable requires study through the lens of implementation science as well as using traditional effectiveness research.

Primary care is optimally suited to play a central role in SUD care transitions because of its geographic reach, team-based care models, greater accessibility relative to specialty SUD treatment, and expertise in chronic disease management. However, patients with SUD may face substantial barriers to transitioning to primary care-based treatment after hospitalization, including cravings, insurance limitations, lack of rapid access to care, unreliable transportation, and unstable housing. Furthermore, primary care clinicians’ (PCP) readiness to provide SUD care is affected by inadequate training, support, and even stigma. Models of care that integrate substance use expertise and interdisciplinary support into primary care environments may simultaneously improve confidence and quality of primary care-based SUD treatment while partnering with acute care settings like hospitals to strengthen care transitions to long-term, comprehensive follow-up [32].

This study’s objective is to evaluate the feasibility of integrating an Interdisciplinary Addiction Care Transition (i.e., IntACT) Team – including a Board-certified addiction specialist, a nurse care manager, and a peer support specialist – into a primary care setting to improve care transitions and retention in SUD treatment following medical hospitalization. Our central hypothesis is that adding interdisciplinary support will be feasible, acceptable, and will improve linkage to and retention in primary care and SUD treatment.

## Methods

### Objectives

The primary objectives of the IntACT pilot randomized controlled trial (RCT) are to: 1) evaluate the implementation of the IntACT team-based intervention, and 2) obtain preliminary measures of effectiveness related to post-hospitalization care linkage and engagement in follow-up treatment, compared to Usual Care (Fig 1). This pilot study will inform the refinement of intervention components and implementation strategies to be studied in a subsequent fully-powered Hybrid Type 2 Implementation-Effectiveness RCT [33,34].

**Fig 1 pone.0359281.g001:**
[figure not shown]
Participant timeline of enrollment, interventions, and assessments. Abbreviations: SF-12 = 12-Item Short Form Survey; TAPS = Tobacco, Alcohol, Prescription Medication, and Other Substances Tool; PHQ-9 = Patient Health Questionnaire-9; GAD-7 = Generalized Anxiety Disorder-7; TLFB = Timeline Follow-Back; IntACT = Interdisciplinary Addiction Care Transition team.

The IntACT trial’s secondary objectives are to measure the intervention’s effects on: 1) time from discharge to first completed follow-up medical or SUD visit, 2) substance use patterns, and 3) rates of acute care utilization (i.e., hospital readmission, emergency department [ED] or urgent care visits). Including a broad range of effectiveness outcomes will help to determine the feasibility of the study’s assessment approach and outcomes selection for a future fully-powered trial.

### Study design

The IntACT pilot study is a single-site RCT that will enroll patients with SUD during an index hospitalization and randomize them to receive IntACT or Usual Care over an intervention period of 4 months (Fig 1) [35]. Randomization is unbalanced, with a ratio of 3:2 favoring the intervention arm over Usual Care. This randomization scheme is intended to prioritize data collection about the feasibility and implementation of IntACT by favoring assignment to the intervention arm. Additionally, we expect IntACT to be superior to Usual Care and therefore have an ethical rationale for more participants receiving the intervention. Finally, unbalanced randomization has only slightly less power than a balanced design when the absolute differences between the groups are small [36,37]. The randomization sequence will be developed by an impartial third party at the University of Utah Clinical and Translational Science Institute using random permuted blocks and embedded into a secure online platform (REDCap). The allocation sequence will be concealed until the time of assignment to IntACT or Usual Care. While the nature of the intervention precludes masking for patients and clinicians, statisticians will be masked to study arm assignment.

### Recruitment and eligibility

Recruitment will occur at a single 425-bed tertiary academic medical center. A total of 75 patients will be recruited. Patient inclusion criteria include: 1) aged 18 years and older, 2) hospitalized at the study site for any medical reason, and 3) Electronic Health Record (EHR) documented diagnosis of any SUD. Exclusion criteria are: 1) currently incarcerated, and 2) Tobacco Use as the only documented SUD. Potential participants will be identified through a combination of clinician referral (i.e., the study will be advertised to hospital clinicians and staff, and hospital care teams and the addiction consult service can refer patients to the study) and prescreening. The prescreening process will consist of the IntACT research coordinator reviewing a curated list of daily hospital admissions filtered to contain new medical admissions with a documented SUD. Admission can be for any medical cause. Patients from the prescreening list that appear to meet eligibility criteria after EHR review will be approached and screened for enrollment.

Additionally, 20 clinicians who interact with IntACT will be recruited from both inpatient and outpatient settings to assess IntACT’s feasibility and acceptability. Clinician inclusion criteria include: 1) aged 18 years and older, 2) provided direct clinical care in any capacity to enrolled patients either in the hospital or in the outpatient setting (e.g., hospitalist, PCP, specialist/consultant), and 3) interact with the IntACT team in a clinical/shared patient care capacity (e.g., coordinated discharge planning). Exclusion criteria include an inability to complete surveys and/or interviews in English or Spanish. Potential participants will be identified through review of clinical EHR notes for enrolled patients and through word of mouth from the IntACT clinical team.

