**Primary Effectiveness Outcomes (compared between intervention and control groups)**				
Care Linkage	% of participants attending an outpatient visit within 14 days of discharge	EHR/admin	LR	Once/patient
Treatment Retention	% of patients with evidence of SUD treatment engagement (e.g., active prescription, visit with associated SUD diagnosis within past month)	EHR/admin	LR	At 2, 4, and 6 months

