**Secondary Effectiveness Outcomes (compared between intervention and control groups)**				
Time to First Visit	Number of days elapsed between discharge and first primary care appt	EHR/admin	LR	Once/patient
Acute Care Utilization	# of ED, hospital, or urgent care visits during the 6 months preceding and 6 months following enrollment	PT	S, Qual	At 2, 4, and 6 months
Substance Use	Self-reported frequency and amount of substance use	PT	S, Qual	At 2, 4, and 6 months

**Abbreviations**: CT = clinical team (PCP, hospitalists, social workers). IT = IntACT team members. S = Survey. Qual = qualitative interviews or focus groups, Admin = administrative data. PT = patient. EHR = electronic health record. LR = logistic/linear regression

Primary effectiveness outcomes will be compared between intervention and control groups and include: 1) the percentage of participants who attend a follow-up visit (e.g., primary care, specialty care, SUD care) within 14 days of discharge, and 2) the percentage of participants with evidence of SUD care engagement at 2, 4, and 6 months following discharge, including attendance at scheduled visits and/or documentation of medication for substance use disorder receipt. Secondary effectiveness outcomes include: 1) time to first follow-up visit after hospital discharge; 2) self-reported substance use; and 3) acute care utilization including hospital readmission, ED visits, and urgent care visits. These outcomes will be assessed using a combination of administrative data review and patient self-report using the Timeline Followback method, an established framework for assessing recent substance use patterns [46,47].

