### Statistical analysis

Consistent with National Institutes of Health recommendations for pilot and feasibility studies, this trial is not designed for statistical power to definitively test effectiveness hypotheses [48]. Quantitative data related to implementation will be presented descriptively. Linear and logistic regression modelling will be used, as appropriate, to compare effectiveness outcomes between the control and intervention groups in order to test the feasibility of our assessment and analytic strategies (Table 2). Complete case analysis will be used as a primary approach to missing data. If there is a large amount of missing data, multiple imputations will be used to mitigate the effects of missing data.

Semi-structured interviews related to IntACT’s implementation will be recorded, transcribed and de-identified. Subsequently, the transcripts will summarized and deductively analyzed according to the domains of the PRISM implementation framework using a Rapid Qualitative Analytic approach [49–51]. Qualitative themes pertaining to intervention implementation will be identified from the summaries and compared with quantitative data to identify cross-cutting themes related to intervention acceptability, appropriateness, and feasibility. Mixed methods research frameworks (e.g., joint display) will be used to draw inferences from the combined quantitative and qualitative implementation data [52,53].

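### The primary retention outcome cannot separate treatment continued from before admission from newly linked treatment, because eligibility takes patients whatever their treatment status and engagement is assessed only at follow-up

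*Protocol article*

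**What the plan says.** Under Recruitment and eligibility, the SUD criterion is an "Electronic Health Record (EHR) documented diagnosis of any SUD". The restrictions that follow do not concern treatment: "Exclusion criteria are: 1) currently incarcerated, and 2) Tobacco Use as the only documented SUD". A patient on stable SUD treatment before admission is eligible, and so is a patient with an old diagnosis and no current treatment.

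Table 2 defines the primary retention outcome as "evidence of SUD treatment engagement (e.g., active prescription, visit with associated SUD diagnosis within past month". The text below the table reports it as "the percentage of participants with evidence of SUD care engagement at 2, 4, and 6 months following discharge". Neither place requires the treatment to be new or to follow from the index stay, and no value before enrollment is mentioned. By contrast, Table 2 counts acute care use over the 6 months before enrollment as well as the 6 months after.

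On allocation, Study design says "Randomization is unbalanced, with a ratio of 3:2 favoring the intervention arm over Usual Care", with the sequence generated "using random permuted blocks and embedded into a secure online platform (REDCap". No stratification factor is mentioned. Statistical analysis says "Linear and logistic regression modelling will be used, as appropriate, to compare effectiveness outcomes between the control and intervention groups" and names no covariate.

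**The concern.** Each choice is reasonable alone. Broad eligibility suits a pragmatic pilot, and current engagement is a practical EHR outcome. Together they produce a retention percentage that mixes two groups: patients whose earlier treatment carried on, and patients connected to treatment through the hospital stay. The article's hypothesis covers both linkage to care and retention in it, and the Discussion presents connecting patients to longitudinal care as the gap to be filled. The outcome as fixed cannot show how much of either occurred.

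Treatment status before admission is likely to predict engagement at follow-up strongly. In arms this small, a chance difference in that status can create or hide part of an apparent effect. If IntACT mainly helps patients not yet in treatment, the pooled difference also understates its effect in them. The pilot's outcomes are meant to inform outcome selection for a fully powered trial, so rates and differences from a mixed population would be unclear planning inputs.

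**Working it through.** **Inputs from the article.** N = 75 at 3:2, so 75 × 3/5 = 45 IntACT and 75 × 2/5 = 30 Usual Care if the ratio is met exactly. The article gives no engagement share, retention rate, effect size, alpha or power, so there is no planned figure to reproduce.

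**Assumed inputs.**
- Share engaged before admission, f: 0.2 to 0.5.
- Retention in patients not engaged at baseline: 0.30 Usual Care, 0.50 IntACT.
- Retention in patients already engaged, r: 0.80 to 1.00, equal in both arms.
- Two-sided alpha 0.05.

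**1. What the outcome can distinguish.** Take one patient whose prescription predates admission and one whose prescription starts at discharge, both active at month 2. Both meet the Table 2 definition, and nothing in the stated outcome tells them apart.

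**2. Chance imbalance.** SD = √[f(1−f)(1/45 + 1/30)].
- f = 0.3: √(0.21 × 0.0556) = 0.108.
- f = 0.4: √(0.24 × 0.0556) = 0.115.

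By the normal approximation, an imbalance above 10 points occurs in about 35% (f = 0.3) to 39% (f = 0.4) of trials. An exact two-binomial calculation for 10 points or more gives 38% and 42%. At f = 0.2 it gives 32%.

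**3. Effect of an imbalance on the unadjusted difference.** Shift = imbalance × gap in retention between engaged and other patients.
- r = 0.80, Usual Care rates: 0.10 × (0.80 − 0.30) = 5 points.
- r = 0.85, Usual Care rates: 0.10 × (0.85 − 0.30) = 5.5 points.
- r = 0.85, with the excess wholly in the IntACT arm: 0.10 × (0.85 − 0.50) = 3.5 points.

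**4. What adjustment gains.** 20,000 simulated trials per f (r = 0.85; 0.30 versus 0.50), with the risk difference from linear regression with and without baseline engagement:

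| f | Mean, unadjusted | SD, unadjusted | Mean, adjusted | SD, adjusted | Variance ratio |
|---|---|---|---|---|---|
| 0.2 | 0.160 | 0.116 | 0.161 | 0.109 | 0.87 |
| 0.3 | 0.139 | 0.117 | 0.141 | 0.106 | 0.83 |
| 0.4 | 0.121 | 0.115 | 0.122 | 0.103 | 0.80 |

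The variance falls by 13%, 17% and 20%. The mean hardly moves, so adjustment improves precision and leaves dilution as it was.

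**5. Dilution.** If engaged patients do equally well in both arms, the pooled difference is (1 − f) × 0.20: 16 points at f = 0.2, 14 at f = 0.3 and 10 at f = 0.5. The planning consequence follows from the usual formula at 3:2 and 80% power, with n₀ the Usual Care arm:

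n₀ = [1.96√(p̄(1−p̄)(1 + 1/1.5)) + 0.8416√(p₀(1−p₀) + p₁(1−p₁)/1.5)]² / (p₁−p₀)²

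At f = 0 (0.30 versus 0.50, p̄ = 0.42), n₀ = 78 and the total is 78 + 117 = 195. Over r = 0.80 to 1.00 the total becomes about 318 at f = 0.2, 403–415 at f = 0.3 and 680–780 at f = 0.5.

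**The case against.** The strongest reply is that much of this belongs to documents not shown. The article condenses a fuller protocol. Covariate lists and stratification factors are often left to that protocol or to the SAP, and a baseline substance use history questionnaire is collected, so adjustment remains open. That stands: the absence of a named covariate is not a fault in itself. A reader might infer that the plan commits to an unstratified, unadjusted comparison, but the article is silent on both.

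A reader might also infer that patients already in treatment count as retained whatever their arm. They do not. They must still show engagement at each follow-up, and IntACT could help keep them in care, which is a proper aim of the trial. Similarly, a patient in remission is not necessarily scored as not retained, since a qualifying SUD-coded visit would count.

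Randomization balances prior treatment in expectation, so the unadjusted comparison is not systematically biased. The trial also disclaims power for definitive effectiveness conclusions, and the gain in precision is modest: at f = 0.3 the 95% half-width goes from 1.96 × 0.117 ≈ 23 points to 1.96 × 0.106 ≈ 21.

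Finally, the gain in the working is on the risk-difference scale. In logistic regression, adding a prognostic covariate changes the target to a conditional odds ratio, and the log-odds standard error does not shrink in the same way. This bears on how the result is reported.

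None of these points removes the core. The eligibility rule and the outcome definition are both fixed in the article, and together they leave continuing and new treatment indistinguishable.

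**Conclusion.** The point holds as a limit on what the retention outcome can show and as an avoidable source of noise. It is not a bias and not a contradiction in the plan. Its size rests wholly on assumed rates. With 30–40% engaged before admission, imbalance has an SD of about 11 points, worth roughly 5 to 6 points on the retention difference at Usual Care rates. A 20-point effect confined to patients not yet in treatment would appear as 14 points at 30% engaged. If few enrolled patients are in treatment, or if IntACT helps treated patients equally, the effect is smaller. The harm falls mainly on the estimates carried into the later trial. This is a worthwhile, cheap improvement.

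**What to change.** Keep eligibility, sample size and the outcome definition unchanged.

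1. In the same EHR extraction, apply the Table 2 engagement definition to the month before the index admission.
2. Pre-specify that yes/no status as a covariate in the retention model. Report a standardized risk difference, so that the precision gain applies to the reported quantity.
3. Tabulate retention by arm within baseline engagement status, descriptively and without subgroup testing. This makes dilution visible and gives the later trial separate rates for continuing and new patients.

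Adjusting the 14-day linkage model is optional. That outcome counts any outpatient visit, including primary and specialty care, and nothing above argues for it.

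The cost is one extra EHR look-back, one covariate in a small model, and imprecise rates by baseline status. At 35% engaged there would be about 16 versus 10 engaged patients. With 80% retained, the standard error of their difference is √(0.16/16 + 0.16/10) ≈ 16 points. No extra patients or visits are needed. The specification should be fixed before outcome data are seen.

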For the clinician cohort, potentially eligible clinicians (i.e., those identified as providing clinical care to intervention patients) will be contacted by study staff either verbally or via secure institutional email and screened for eligibility based on inclusion/exclusion criteria. If eligible, research staff will assess interest in participation and conduct a formal informed consent process for those who wish to enroll. To minimize any possibility of undue influence, clinician recruitment will be conducted by the research coordinator or study staff, not by supervising physicians or direct clinical colleagues.

In addition to recruitment and enrollment, study procedures also involve iterative assessment of primary and secondary study outcomes (Table 1). Outcome assessment will be led by study staff and take place at scheduled in-person study visits or, if necessary, remotely over telephone or videoconferencing. These assessments will consist of a series of surveys and occur at baseline, 2, 4, and 6 months after randomization. Patient participants will be compensated $35 for completing each of the first three assessments (i.e., baseline, 2 month, 4 month) and $75 for completing the final 6-month close-out visit (total potential earnings $180). Purposive sampling will be used to recruit fifteen intervention participants who completed the final close-out visit to participate in a 45-minute semi-structured interview about their experience with IntACT. Compensation for completing the interview will be $75. If a participants misses study assessment visits, they will still be invited to conduct a study close-out visit at six months and complete the end of study survey.

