Enrolled clinicians will complete an implementation survey after each exposure to IntACT (e.g., IntACT assists with discharge planning for a patient that they are caring for in the hospital). These surveys will use validated tools to assess the feasibility, acceptability, and appropriateness of IntACT, its specific components, and its implementation strategies from a clinician’s perspective. Purposive sampling will be used to recruit a subset of twelve clinicians who had extensive interactions with IntACT to complete semi-structured interviews further exploring experiences and perceptions related to the intervention. IntACT team members (n = 3) will be surveyed and interviewed one time at the end of the study period using these same assessment tools. IntACT team members will also complete a fidelity checklist one time for each new intervention patient enrollment documenting the clinical and psychosocial services provided. Clinician participants will be compensated $30 for completing each survey and an additional $75 for completing a 45-minute semi-structured interview.

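### The IntACT team can name some of the clinicians who rate it, and clinician interviews are limited to high-exposure clinicians, so clinician-rated primary implementation outcomes carry a risk of favourable selection

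*Protocol article*

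**What the plan says.** Under Recruitment and eligibility, the article states that "20 clinicians who interact with IntACT will be recruited from both inpatient and outpatient settings". It gives two ways of finding them: by reviewing enrolled patients' notes in the health record, and "through word of mouth from the IntACT clinical team". No split between the two routes is given.

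Under Procedures and assessments, contact, screening and consent belong to study staff: "clinician recruitment will be conducted by the research coordinator or study staff, not by supervising physicians or direct clinical colleagues". The stated purpose is "To minimize any possibility of undue influence".

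The same section sets out two kinds of clinician data. For the surveys, "Enrolled clinicians will complete an implementation survey after each exposure to IntACT", with no minimum amount of contact. For the interviews, the plan is to "recruit a subset of twelve clinicians who had extensive interactions with IntACT to complete semi-structured interviews". The three IntACT team members are surveyed and interviewed with the same tools, and fifteen intervention patients who completed the close-out visit are also interviewed.

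The Outcomes section lists feasibility, acceptability and appropriateness among the primary implementation outcomes. The Statistical analysis section says that quantitative implementation data will be described, without a comparison. The Limitations section concedes social desirability bias and other potential confounders in subjective measures, but does not mention how raters are chosen.

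**The concern.** A descriptive rating with no comparator is only as good as the sample of raters. Here the team whose work is rated may help decide who rates it. A team asked for names may more readily think of colleagues with whom the collaboration went well.

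The interview rule adds a second filter. Twelve of 20 clinicians are interviewed, all from the high-exposure end. Clinicians who had little contact, or for whom the contact did not develop, are left out of the component meant to explain the ratings.

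The stated aim of the pilot is to refine the intervention and its implementation strategies before a fully powered trial. If both filters favour satisfied users, the pilot would report higher acceptability than clinicians in general would give, and could miss barriers that the larger trial will meet.

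**Working it through.** There is no planned figure to reproduce: the article gives no target or threshold for the clinician ratings. The check is a reading of the text followed by illustrative arithmetic.

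**Which step each rule covers**

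| Step | Who or what decides | Open to the rated team? |
|---|---|---|
| Identification | Chart review and team word of mouth | Yes, in part |
| Contact, screening, consent | Research coordinator or study staff | No |
| Survey | Every enrolled clinician, after each exposure | Only through identification |
| Interview | 12 clinicians with extensive contact | Through identification, then the exposure rule |

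The safeguard covers the second step. Nothing covers the first.

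**Does it matter who is named?** Randomization is 3:2 among 75 patients, so 75 × 3/5 = 45 receive IntACT. Each may have inpatient and outpatient clinicians. If the eligible pool exceeds 20, which is likely but not stated, the choice of the 20 affects the result. The interviews take 12/20 = 60% of the clinicians.

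**Possible shift in the survey mean.** Let w be the share of the 20 who were team-named, and d the mean rating of team-named clinicians minus that of chart-identified clinicians. Then

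observed mean = (1 − w) × m + w × (m + d) = m + w × d,

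where m is the mean among chart-identified clinicians. The shift is w × d. The values of w and d, and a 1 to 5 scale, are assumptions:

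| d | w = 25% | w = 50% | w = 75% | w = 100% |
|---|---|---|---|---|
| −0.25 | −0.06 | −0.125 | −0.19 | −0.25 |
| 0 | 0 | 0 | 0 | 0 |
| 0.25 | 0.06 | 0.125 | 0.19 | 0.25 |
| 0.5 | 0.125 | 0.25 | 0.375 | 0.50 |
| 1.0 | 0.25 | 0.50 | 0.75 | 1.00 |

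**Comparison with sampling error.** The 95% half-width for a mean of 20 ratings is 1.96 × SD / √20. For assumed SDs of 0.6, 0.8 and 1.0 it is 0.26, 0.35 and 0.44.

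Under moderate assumptions (w = 50%, d = 0.5) the shift of 0.25 is about as large as the half-width at the smallest SD. Under d = 0 there is none, and under negative d it runs the other way. The table shows what is possible, not what will happen.

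**The case against.** The strongest reply is that this is an ordinary sampling choice in a small descriptive pilot. Interviewing people with enough contact to describe an intervention is accepted qualitative practice. Chart review is a separate identification route, every enrolled clinician is surveyed whatever their exposure, and no acceptability threshold is stated that a shifted mean could cross. Table 2 also lists patients and team members as sources for these outcomes, and feasibility draws on study enrollment as well.

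Most of this stands, and it rules out several stronger readings that a reader might infer:

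- **That the ratings are biased upward.** The article gives neither the share of team-named clinicians nor any rating gap. Clinicians with extensive contact may also see more problems.
- **That team naming defeats the recruitment safeguard.** The safeguard concerns undue influence at approach and consent, and remains intact there. It simply does not reach identification.
- **That only heavy users rate IntACT.** The exposure rule applies to the 12 clinician interviews alone.
- **That clinicians left out of the interviews tried IntACT and gave it up.** Clinicians meet IntACT through patients assigned to it, so low exposure may only mean few such patients.
- **That the health record offers a complete, unbiased list.** Follow-up may take place at a clinic of the patient's choosing, and nothing says that such notes reach the site's record. Word of mouth may be the only way to find those clinicians.

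The reply does not remove the two facts at issue: the rated team may supply some of its raters, and the clinician interviews leave out the low-exposure end. The Outcomes text assigns the validated instruments to clinicians and team members. The patient schedule in Table 1 shows no such instrument, only the interviews. Patient data may therefore do little to offset selection in the quantitative ratings.

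**Conclusion.** The concern holds as a risk of selection in the clinician-rated acceptability, appropriateness and feasibility results. A favourable direction is plausible, but neither direction nor size follows from the article. Under the assumed inputs the shift runs from −0.25 to +1.0 point on a 5-point scale, against a 95% half-width of 0.26 to 0.44. It could therefore be nil or could match or exceed the sampling error.

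This does not invalidate the trial and does not touch the effectiveness comparison between arms. It makes a primary implementation result hard to interpret, because a reader could not tell how far high ratings reflect the intervention and how far they reflect who was asked. It is worth settling before the first clinician is invited, since the identification route may be hard to reconstruct afterwards.

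**What to change.** 1. Have the research coordinator build the primary invitation list from health-record notes of intervention patients. Invite clinicians consecutively by date of first IntACT contact, across inpatient and outpatient settings.
2. Keep team word of mouth only as a supplement for clinicians not visible in the record, such as those at outside community sites.
3. Record each clinician's identification route and the number approached by each route, and report ratings by route.
4. Choose the 12 clinician interviews to include some low-exposure and some low-scoring clinicians alongside high-exposure ones.
5. Name rater selection in the limitations.

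The cost is slightly more chart review and fewer interviews with the most exposed clinicians. With 20 clinicians the by-route summaries will be imprecise and should be read as descriptive only.
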